# Study protocol: Type III hybrid effectiveness-implementation study implementing Age-Friendly evidence-based practices in the VA to improve outcomes in older adults

**DOI:** 10.1186/s43058-023-00431-5

**Published:** 2023-05-25

**Keywords:** Implementation science, Veterans Health Administration, Veterans, Age-friendly, Geriatrics, Age-friendly healthcare system

## Abstract

**Background:**

Unmet care needs among older adults accelerate cognitive and functional decline and increase medical harms, leading to poorer quality of life, more frequent hospitalizations, and premature nursing home admission. The Department of Veterans Affairs (VA) is invested in becoming an “Age-Friendly Health System” to better address four tenets associated with reduced harm and improved outcomes among the 4 million Veterans aged 65 and over receiving VA care. These four tenets focus on “4Ms” that are fundamental to the care of older adults, including (1) what *M*atters (ensuring that care is consistent with each person’s goals and preferences); (2) *M*edications (only using necessary medications and ensuring that they do not interfere with what matters, mobility, or mentation); (3) *M*entation (preventing, identifying, treating, and managing dementia, depression, and delirium); and (4) *M*obility (promoting safe movement to maintain function and independence). The Safer Aging through Geriatrics-Informed Evidence-Based Practices (SAGE) Quality Enhancement Research Initiative (QUERI) seeks to implement four evidence-based practices (EBPs) that have shown efficacy in addressing these core tenets of an “Age-Friendly Health System,” leading to reduced harm and improved outcomes in older adults.

**Methods:**

We will implement four EBPs in 9 VA medical centers and associated outpatient clinics using a type III hybrid effectiveness-implementation stepped-wedge trial design. We selected four EBPs that align with Age-Friendly Health System principles: Surgical Pause, EMPOWER (Eliminating Medications Through Patient Ownership of End Results), TAP (Tailored Activities Program), and CAPABLE (Community Aging in Place – Advancing Better Living for Elders). Guided by the Pragmatic Robust Implementation and Sustainability Model (PRISM), we are comparing implementation as usual vs. active facilitation. Reach is our primary implementation outcome, while “facility-free days” is our primary effectiveness outcome across evidence-based practice interventions.

**Discussion:**

To our knowledge, this is the first large-scale randomized effort to implement “Age-Friendly” aligned evidence-based practices. Understanding the barriers and facilitators to implementing these evidence-based practices is essential to successfully help shift current healthcare systems to become Age-Friendly. Effective implementation of this project will improve the care and outcomes of older Veterans and help them age safely within their communities.

**Trial registration:**

Registered 05 May 2021, at ISRCTN #60,657,985.

**Reporting guidelines:**

Standards for Reporting Implementation Studies (see attached).

**Supplementary Information:**

The online version contains supplementary material available at 10.1186/s43058-023-00431-5.

Contribution to the literature
Veterans aged 65 and older who do not receive age-friendly care are at increased risk for poor outcomes.The Age-Friendly Health System model of What Matters, Medications, Mentation, and Mobility (4Ms) is an evidence-based framework for ensuring older adults receive holistic care that aligns with their wishes.Studies have not evaluated the adoption of 4Ms care on a large scale within a national health care systemThis study will evaluate the implementation of four EBPs across nine VA medical centers to assess EBP “Reach” and facility-free days.

## Background

Older adults have needs that are not being met by the current health care system [1, 2]. As medical complexity and functional impairment among older populations increase, health systems increasingly struggle to provide high-quality, goal-concordant care [1–3]. Inappropriate care and unmet care needs among older adults accelerate cognitive and functional decline, leading to poorer quality of life, more frequent hospital utilization, and premature nursing home admission [1, 2]. Recognizing persistent quality gaps in care for older adults nationally, the Institute for Healthcare Improvement (IHI) and The John A. Hartford Foundation are leading a national campaign to make health systems “Age Friendly” [3–6].

The Age-Friendly Health System (AFHS) model is a patient-centered framework that incorporates evidence-based elements of high-quality care by focusing on “4Ms” that are fundamental to the care of older adults (Fig. 1). These include (1) what *M*atters (ensuring that care is consistent with each person’s goals and preferences); (2) *M*edications (only using necessary medications and ensuring that they do not interfere with what matters, mobility, or mentation); (3) *M*entation (preventing, identifying, treating, and managing dementia, depression, and delirium); and (4) *M*obility (promoting safe movement to maintain function and independence) [1, 2, 4–6]. For this model to be successful, there is a critical need to understand how to implement and sustain AFHS at scale [5]. To date, the evidence regarding AFHS implementation best practices is limited to case studies [7, 8]. Furthermore, it is unclear which of the 4 M-concordant interventions are most impactful for the outcomes of older adults who dwelling in the community [3, 4, 9–12].

**Fig. 1 Fig1:**
[figure not shown]
The Institute for Healthcare Improvement model of Age-Friendly Health Systems

With more than 4 million Veterans aged 65 and older [13], the VA is a promising context for implementation of the AFHS model. The Safer Aging through Geriatrics-Informed Evidence-Based Practices (SAGE) Quality Enhancement Research Initiative (QUERI) program, funded by VA QUERI, is intended to address these gaps. This program aims to test different implementation strategies while implementing four evidence-based practices (each aligned with one of the 4Ms) across nine VA medical centers and their associated community-based outpatient clinics with in the Veteran Integrated Service Network (VISN) 4 (*see map—*https://www.visn4.va.gov/VISN4/locations/map.html).

### Study goals and objectives

Our goals in the SAGE QUERI are threefold: (1) to compare different implementation strategies in a randomized fashion to understand how the interaction between implementation strategies, local site context, and intervention characteristics lead to different implementation outcomes; (2) to measure the impact of the implementation of evidence-based practices (or EBPs) on outcomes of older Veterans who are community dwelling; and (3) understand how these EBPs can most successfully be adapted for the VA context to allow successful national dissemination and maintenance in clinical practice.

### Conceptual framework and theoretical foundation

Our approach builds on the AFHS conceptual framework supported by IHI and The John A. Hartford Foundation [3, 6]. We are employing the Practical, Robust Implementation and Sustainability Model (PRISM) as a theoretical foundation to guide our pre-implementation assessment and implementation evaluation (Table 1 and Fig. 2; [14]). PRISM draws upon and integrates key concepts from Diffusion of Innovations Theory, IHI quality improvement models, and the Chronic Care Model [14, 15]. PRISM is an extension of the original Reach Effectiveness-Adoption Implementation Maintenance (RE-AIM) evaluation model [14, 15].

**Table 1 Tab1:** Assessing PRISM domains to understand context for implementation

PRISM domain	What we are assessing	Data collection techniques
Organization perspectives and values	- Staff perspectives evidence base - Staff perspectives usefulness in local context - Current workflow processes - How each EBP fits into the broader organization - Potential contextual factors that may facilitate/limit implementation - Job satisfaction	- Key informant interviews - Site visit rapid ethnography observations - Staff process mapping - Brainwriting activity - VA all employee surveys (for example SAIL ratings)
Patient perspective and values	- Veteran perspectives on key intervention components - Overall program satisfaction with care - Identify potential unmet needs	- Site visit rapid ethnography observations - Veteran Advisory Board feedback - SAIL metrics
Organizational recipient characteristics	- Existing quality gaps documented by data and as perceived by staff - Organizational priorities as perceived by frontline staff and leaders - Staffing and turnover - Interfacility communication - Existing quality improvement initiatives	- National level VA quantitative data - VA all employee surveys - Key informant interviews - Brainwriting activity
Patient recipient characteristics	- Sociodemographic characteristics - Health status - Competing programs or demands on patients - Stories of patients who could be impacted by AFHS - Overall program satisfaction with care	- National level VA quantitative data - Site visit rapid ethnography observations - Veteran Advisory Board feedback
Implementation and sustainability infrastructure	- Existing processes and systems - Prior experience with new initiatives - Culture regarding satisfaction with work and new initiatives - Relationships between key stakeholders - Resources for implementation and sustainment - Staff readiness to change	- Key informant interviews - Brainwriting activity - Staff process mapping
External environment	- Current regulatory environment as perceived by staff/leaders - Changes in organization due to external changes (MISSION, changing patient population, reimbursement) - Existing guidelines or incentives	- Key informant interviews - Brainwriting activity - Review of artifacts - VA all employee surveys - National level VA quantitative data

**Fig. 2 Fig2:**
[figure not shown]
The Pragmatic Robust Implementation and Sustainability Model [14]

PRISM provides a useful framework for assessing implementation barriers and facilitators and has been used to evaluate multiple VA and non-VA health systems interventions [15–21]. Attention to PRISM “Contextual Factors” are being used to focus and organize pre-implementation site assessment on specific domains (Fig. 2 and Table 1). These contextual factors include internal factors (e.g., multiple level organizational patient characteristics, multiple level organizational patient perspectives, implementation and sustainability infrastructure) and external factors (e.g., policy, resources, guidelines, incentives). To tailor the implementation strategies at each site, the concept of “Fit” (Fig. 2) will guide proactive planning of what was learned in the pre-implementation assessment—such as attention to inner and outer context—to what is known about the intervention components.

The PRISM model also highlights the key interplay between implementation strategies and EBPs and calls for ongoing evaluation (using RE-AIM) to generate feedback during the study. We operationalize RE-AIM (Table 2) as the following: *Reach* (proportion of eligible population receiving each EBP), *Effectiveness* (evidence of effects on health outcomes), *Adoption* (proportion of clinical sites or teams implementing the EBP), *Implementation* (fidelity to the EBP and adaptations made), and *Maintenance* (what proportion of sites continue to use the EBPs after active implementation ceases). Additionally, we plan incorporate “Overarching Issues” (Fig. 2) to better understand “how” and “why” implementation did or did not work. RE-AIM emphasizes the importance of tracking adaptations, identifying the representativeness of the sample, and evaluating costs and benefits [22]. This framework informs the entire implementation process.

**Table 2 Tab2:** Reach, Effectiveness, Adoption, Implementation, Maintenance (RE-AIM) outcome

Construct	Definition [22]	SAGE outcomes
Reach	The number or proportion of people who participate in the intervention	Proportion of eligible Veterans who receive each EBP
Effectiveness	The effect of the intervention on relevant outcomes (e.g., quality of life, economic outcomes)	Facility-free days: the number of days an older Veteran remains alive and outside the hospital or nursing home
Adoption^a^	The number or proportion of sites or individuals who are willing to initiate the program	Proportion of VA Medical Center (or service line) who begin implementation of the EBP
Implementation^a^	Fidelity to the core components of the intervention	Of adopting sites, proportion of EBP interactions that complete 80% or more of EBP core components
Maintenance^a^	Sustainment of the program or behavior over a period of 6 months	Of adopting sites, proportion of eligible Veterans enrolled in EBP is stable at 1 year follow-up

^a^SAGE QUERI secondary outcomes

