Core components	• Prior to surgical decision making, patient completes the RAI • Patients with RAI ≥ 37 referred for goal clarification conversation • Clinician(s) and patient review treatment plan, with or without surgery, to align with patient’s overarching goals and values	• Identifying patient panel • Mail EMPOWER brochure which includes a self-assessment of risks for medication, presentation of evidence of harms, medication education, and suggestions for conversation with provider • Provider prescriber education	• OT formal training • OT conducts home assessment to identify Veterans’ preserved capabilities and interests • OT develops 3 tailored activity prescriptions • Caregiver and Veteran participate in at least 3 TAP sessions	• OT and nurse formal training • Staffing components: • OT assess functional abilities, home accessibility, and safety then collaborates with Veteran to create up to 3 ADL/IDAL goals • Nurse—assesses medical status and develops 3 nursing goals • Handy Person—completes home modifications/repairs
Example adaptations	• Which staff screen • Strategy for communicating results to surgeon • In-person versus virtual training • Which clinician completes goal clarification conversation	• Format of brochure • Timing of brochure mailing and communication with prescriber • Which staff mail the brochure • Number of mailings	• Other health professionals (social worker, psychologist, RN) may also implement TAP with OT supervision • Location of session • Number of visits	• Referral source • Addressing more critical and expensive home repairs • Number of sessions conducted virtually vs in home after the initial assessment
Patient eligibility	• Age 65 + • RAI ≥ 37 • Considering “major surgery” as defined by a VASQIP-eligible CPT code	• Age 65 + • Community-dwelling (i.e., not residing in a nursing home) • Receiving a prescription for a targeted drug class for at least 90 of the last 120 days from a VA prescriber	• Age 65 + • Has a dementia diagnosis • Has an adult caregiver willing/able to participate • Can participate in at least two basic ADLs	• Age 65 + • Low income • At least 1 ADL or 2 IADL deficiencies • Able to ambulate around house independently with or without an assistive device
Potential setting	Preoperative clinics (e.g., surgery, anesthesia, primary care, medical subspecialties)	Primary care, mental health	Home care, home-based primary care, caregiver support program	Home care

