#### Intervention tailoring

Intervention tailoring involves prespecifying changes able to be made to the EBP to support implementation in the local context. This allows for each of the four EBPs to have some degree of adaptability to the local context while still maintaining fidelity. As shown in Table 3, a priori, we defined which aspects of the EBPs are “core” (cannot be modified) and which are “adaptable” (can be tailored to fit local context) to support all RE-AIM outcomes [60]. Based on the findings from the pre-implementation phase, we will work with the EBP developers to help re-define the adaptable elements to tailor the interventions to each site.

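### With three or four core components per EBP in Table 3, the 80% fidelity cut works as all-or-none, and in TAP the core and adaptable lists overlap

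*Protocol article*

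**What the plan says.** Table 2 gives the Implementation outcome, footnoted as secondary, as "Of adopting sites, proportion of EBP interactions that complete 80% or more of EBP core components". The unit is the interaction and the threshold is 80%.

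The components are listed in the core-components row of Table 3. The Intervention tailoring section refers to that table as the place where core and adaptable elements were set in advance: "we defined which aspects of the EBPs are “core” (cannot be modified) and which are “adaptable". The same section says that tailoring leaves fidelity intact.

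For TAP, the core row includes an OT-led home assessment, "OT develops 3 tailored activity prescriptions" and "Caregiver and Veteran participate in at least 3 TAP sessions". The TAP adaptations row includes "Other health professionals (social worker, psychologist, RN) may also implement TAP with OT supervision" and also lists the number of visits.

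**The concern.** An 80% threshold tells the reader that an interaction may fall somewhat short and still count as faithful. With only three or four components there is no value between 75% and 100%, so no shortfall is possible. A low Implementation result could then mean widespread poor delivery or single omissions in otherwise complete interactions, and the reader could not tell which.

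TAP adds a second problem. If an element appears as core in one row and as open to adaptation in another, a scorer can reach opposite results for the same interaction. Because the cut leaves no slack, one disputed item decides the outcome. This matters because the third study goal is to learn how the EBPs can be adapted, and the RE-AIM description places both fidelity and adaptations under Implementation.

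**Working it through.** The plan derives no figure for this outcome, so there is none to reproduce. The check is to count the components and find the smallest number that meets the cut.

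**Rule.** With k components, an interaction that misses one scores (k − 1)/k. This is at least 0.80 only if k is 5 or more.

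**Counts from Table 3.**
- Surgical Pause, 3: the RAI ("Prior to surgical decision making, patient completes the RAI"), referral for goal clarification, treatment plan review.
- EMPOWER, 3: panel identification, the brochure, prescriber education.
- TAP, 4: OT training, home assessment, prescriptions, sessions.
- CAPABLE, 4: training, OT, nurse, and "Handy Person—completes home modifications/repairs". This reads the Staffing components line as a heading over the last three.

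| EBP | k | 0.8 × k | Needed | Score with one miss |
|---|---|---|---|---|
| Surgical Pause | 3 | 2.4 | 3 of 3 | 67% |
| EMPOWER | 3 | 2.4 | 3 of 3 | 67% |
| TAP | 4 | 3.2 | 4 of 4 | 75% |
| CAPABLE | 4 | 3.2 | 4 of 4 | 75% |

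**Other ways to count.** If the Staffing components line is scored as an item, CAPABLE has k = 5 and 4 of 5 = 80% passes. If only its top-level lines count, k = 2 and both are needed. If the four contents of the EMPOWER brochure are scored separately, k = 6 and 5 of 6 = 83% passes. An EMPOWER interaction without prescriber education therefore fails on three items (67%) and passes on six (83%).

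**Illustrative size.** Assume each component is completed independently with probability p. The documents give no value for p.
- All complete: p^k.
- At most one miss: p^k + k·p^(k−1)·(1 − p).

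| p | k = 3, all | k = 3, one miss allowed | k = 4, all | k = 4, one miss allowed |
|---|---|---|---|---|
| 0.90 | 0.729 | 0.729 + 3 × 0.81 × 0.1 = 0.972 | 0.656 | 0.656 + 4 × 0.729 × 0.1 = 0.948 |
| 0.80 | 0.512 | 0.512 + 3 × 0.64 × 0.2 = 0.896 | 0.410 | 0.410 + 4 × 0.512 × 0.2 = 0.819 |

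For CAPABLE at p = 0.90, moving from 4 counted items (4 of 4 needed) to 5 (4 of 5 needed) changes the pass share from 0.656 to 0.919.

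**TAP, scored literally.** If another professional under OT supervision does the assessment, 1 of 4 items is missed (75%, fail). If that person also writes the prescriptions, 2 of 4 are missed (50%, fail). If the number of visits is adapted to fewer than 3 sessions, 1 of 4 is missed (75%, fail). In the other three EBPs, the listed adaptations leave every core item achievable.

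**Removing staff- and site-level items does not restore a tolerance.** Without formal training and prescriber education the counts are 3, 2, 3 and 3, and one miss gives 67%, 50%, 67% and 67%.

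**The case against.** The strongest reply is that Table 3 is a summary in a condensed article, and that a scoring form in the full protocol may list more items. That is a fair limit on the claim about every EBP. CAPABLE prints five bullets and EMPOWER can be split into six items, and either count restores a tolerance of one miss. But the article itself names Table 3 as showing the core components. The higher counts require scoring a heading as a component, or treating the contents of one mailed brochure as separate actions.

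An all-components criterion is also a valid, if strict, measure of fidelity. Adaptations are tracked elsewhere, and follow-up site visits serve as a further check. This stands: the fault lies in the label and the missing tolerance, and one should not infer that fidelity as a whole is misreported.

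The TAP rows can be read as compatible: the OT keeps the assessment and prescriptions while others deliver sessions, and visits vary but stay at three or more. That reading is possible, but the text does not settle it.

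Several stronger readings are tempting and are not supported:
- That the measure penalises adaptation in general. The overlap appears only in TAP and depends on literal scoring.
- That a Veteran screened with RAI below 37 scores 1 of 3. Table 3 makes RAI of at least 37 an eligibility criterion, so this arises only if screening alone counts as an interaction.
- That one training or education gap fails every interaction at a site. A trained clinician, or a Veteran who was identified and mailed the brochure, can be credited interaction by interaction.

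Finally, the pass shares rest on independence. Many of the steps are sequential, so completion is probably correlated.

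**Conclusion.** The concern holds in a limited form. On the natural count of Table 3, the stated 80% threshold is a 100% threshold for all four EBPs; for CAPABLE this depends on reading the Staffing components line as a heading. That part is arithmetic and needs no assumption about completion rates. The effect on the reported proportion cannot be known from the documents. Under independent completion at 80% to 90% per component, the gap between all-or-none and one permitted miss is about 24 to 38 percentage points with three components (0.972 − 0.729; 0.896 − 0.512) and 29 to 41 with four (0.948 − 0.656; 0.819 − 0.410). These figures illustrate the scale and do not predict this trial's result.

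The TAP overlap is a separate and narrower point: the core and adaptable cells allow opposite scores for the same interaction. A reader might infer that a TAP site using the supervised model would score zero. That requires every interaction there to be scored literally and none to have the OT perform the core tasks, which the documents do not say.

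Implementation is a secondary outcome. Reach and facility-free days are unaffected.

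**What to change.** - In Table 2, replace the 80% cut with two summaries for each EBP among adopting sites: the mean percentage of applicable core components completed per interaction, and the proportion of interactions completing all of them. If a single figure is preferred, keep the present criterion and relabel it as all core components completed.
- State the counted components for each EBP. Say whether the CAPABLE staffing line is a heading, whether the EMPOWER brochure is one item, and when an item is not applicable to a Veteran.
- Report formal training and prescriber education separately, at staff or site level, from the Veteran-level items.
- Reconcile TAP's core and adaptable cells with the Intervention tailoring section, so that the scoring of each permitted adaptation is unambiguous. Which reading applies is for the sponsor and the EBP developers to settle.

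The cost is a reworded table row and scoring form, applied to component-level data that the present outcome already needs. The downside is that, with two summaries, fidelity no longer reduces to one 80% figure.
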